# Capecitabine metronomic chemotherapy for metastatic colorectal cancer patients reaching NED: A protocol for a prospective, randomized, controlled trial

**DOI:** 10.1371/journal.pone.0320591

**Published:** 2025-04-21

## Abstract

**Introduction:**

An increasing number of patients with metastatic colorectal cancer (mCRC) have achieved no evidence of diseases (NED) status after surgery or other treatments. However, the latest guidelines for colorectal cancer do not recommend an appropriate treatment for patients with mCRC who achieve NED status. Capecitabine metronomic chemotherapy has the advantages of significant efficacy and minimal adverse reactions, it is a potential effective method for maintenance treatment for mCRC, but no RCTs have been reported. Therefore, we designed a randomized controlled trial to evaluate the efficacy and safety of capecitabine metronomic chemotherapy for mCRC patients who achieve NED.

**Methods/design:**

This study is a prospective, randomized controlled study that evaluates the efficacy and safety of capecitabine metronomic chemotherapy for patients with mCRC who achieve NED status. 240 eligible participants will be randomly assigned to either a capecitabine metronomic chemotherapy group or a “watch and wait” group at a 1:1 allocation ratio. Eligible patients diagnosed with stage IV mCRC, both the primary tumor and the metastases, are those who have achieved R0 resection (or complete destruction by ablation) and reached NED. Participants who are enrolled in the capecitabine group will receive capecitabine (500 mg/m^2^ body surface area twice daily) for 2 years. Meanwhile, those who are assigned to the control group will receive regular imaging examination and follow-up only. All participants will follow up for 1 year after receiving 2 years of intervention. The primary outcomes will be disease-free survival (DFS) from randomization, stratified by preoperative chemotherapy, metastatic organs, number of metastases, lenght of previous systemic treatment, response to previous chemotherapy. Secondary outcomes will include overall survival (OS), 1-year,2-year,3-year survival rate and adverse reactions.

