## Introduction

Metastatic colorectal cancer (mCRC) accounts for more than 40% of the total colorectal cancer population [1,2]. In recent years, with the progress of surgery and a series of drugs to improve the objective response rate of tumors, more and more patients with mCRC can now receive surgical resection after conversion therapy, or achieving no evidence of disease (NED) status through local treatment such as ablation [3,4]. This has greatly improved survival for patients with mCRC. At present, a total of 6 months of perioperative chemotherapy is routinely recommended for patients with mCRC after resection, but many patients have postoperative recurrence and metastasis. For patients with mCRC who achieve NED status after resection, how to avoid tumor recurrence and metastasis after surgery is an urgent clinical problem [5,6].

Approximately 60–70% of patients diagnosed with stage IV colorectal cancer will experience tumor recurrence and metastasis following surgical intervention. Previous studies(JCOG0603, EORTC40983) have demonstrated that adjuvant chemotherapy following surgical intervention for metastatic colorectal cancer is associated with a prolonged duration of disease-free survival (DFS); however, no significant enhancement in overall survival has been observed [7,8]. The presence of Minimal Residual Disease (MRD) or Circulating Tumor Cell (CTC) significantly contributes to the postoperative recurrence of colorectal cancer. The efficacy of adjuvant chemotherapy may be compromised by drug resistance and the immunosuppressive microenvironment within the human body, necessitating the development of novel therapeutic approaches.

Fluorouracil (5 - FU) is the most important and basic drug used in chemotherapy for colorectal cancer. Capecitabine is an oral drug and a member of the fluorouracil class. The highly expressed thymidine phosphorylase in tumor tissue can degrade it into 5-FU, significantly increasing the drug concentration at the tumor site, and simulating continuous perfusion of 5-FU, so that it maintains a stable blood drug concentration at the action site [9]. Single-agent capecitabine is commonly administered to mCRC patients who exhibit intolerance towards multi-drug combination chemotherapy. However, the conventional dosage (Capecitabine 1250mg/m^2^ body surface area twice daily) poses challenges such as significant toxic reactions, immunosuppression, and drug resistance [10,11].

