### Study subjects

All subjects will be recruited through posters at Zhongshan Hospital of Traditional Chinese Medicine Affiliated to Guangzhou University of Chinese Medicine.It will be conducted from December 2021 to December 2025.All subjects must be medically fit patients with mCRC advanced colon cancer who had achieved NED status after surgery or ablation, aged 18–80 years, and with an ECOG score of 0–1, and who have completed perioperative chemotherapy. Major exclusion criteria are multiple primary carcinoma patients; pregnant women; mentally ill patients; patients with other serious underlying diseases. Complete inclusion and exclusion criteria are outlined in Table 1.

**Table 1 pone.0320591.t001:** Study inclusion and exclusion criteria.

Inclusion criteria	Exclusion criteria
(1) Male or female aged 18–80 years.	(1) Patients diagnosed with more than one malignancy.
(2) Pathologically confirmed metastatic colorectal adenocarcinoma.	(2) Pregnant or lactating women.
(3) Contrast-enhanced CT or MRI of the chest and abdomen at the initial diagnosis, clinical stage IV colon cancer with liver and/or lung metastasis, and potentially curative R0 resection (including local therapy such as radiofrequency ablation) for the primary tumor and metastatic lesions, have completed perioperative chemotherapy, and achieved NED status on chest and abdomen CT or MRI within 4 weeks before enrollment.	(3) Patients with mental illness.
(4) ECOG score of 0–1.	(4) Combined with coronary heart disease, myocardial infarction, renal failure, pulmonary embolism and other diseases that may affect the survival of patients.
(5) There were no other underlying diseases affecting organ function.	(5) Patients with poor compliance can not cooperate with the treatment.
(6) Understand, be willing to give consent, and sign the written ICF prior to undergoing any study-specific procedure.	(6) There is a known deficiency of DPD, or Capecitabine intolerance.

Abbreviation: NED, no evidence of disease; ECOG, Eastern Co-operative Oncology Group; ICF, informed consent form; DPD, dihydropyrimidine dehydrogenase.

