### Intervention

The interventions studied will be implemented by attending physicians with at least 3 years of clinical experience in the Oncology Department at Zhongshan Affiliated Hospital, Guangzhou University of Chinese Medicine. Based on chemotherapy theory for metastatic colorectal cancer and previous randomized controlled trials, capecitabine chemotherapy process interventions will be developed under the consensus of colorectal cancer oncology experts. Prior to initiating the study, the clinical practitioner will receive specialized training to gain a comprehensive understanding of capecitabine metronomic chemotherapy, and to administer treatment in accordance with the specific requirements of the investigator’s manual. All eligible patients in both groups will have been diagnosed with stage IV colon cancer with hepatic and/or lung metastases, have potentially cured R0 resection of the primary tumor and metastatic lesion (including local treatments such as radiofrequency ablation), have completed perioperative chemotherapy, and have reached NED status on computed tomography (CT) or MRI within 4 weeks of enrollment. The study will be conducted over a 3-year period, with all treatments completed within the first 2 years. Follow-up will last for 12 months, beginning after the completion of the 24-month intervention period.

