#### Survival rate (DFS and OS).

After visits at the time nodes specified in the trial, patient survival will be calculated at the time nodes of the 1^st^ year, 2^st^ year and the 3^nd^ year after randomization.

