### Quality control, data management and monitoring

Prior to recruitment, research team members will be required to attend a training workshop to ensure their strict adherence to the research protocol, and that they have a comprehensive understanding of the trial management process. The intervention will be implemented by attending physicians with at least 3 years of hospital experience. The trial process will be conducted in accordance with a researcher’s manual of standard operating procedures developed in consultation with experts with extensive therapeutic experience. To improve compliance, we maintained contact with the subjects and at least one family member of the subjects, and regular telephone follow-up was conducted.

This data will be collected and recorded on CRF. All data will be input to a password-protected computer by a staff member who does not know how the group assignments were made. It will be checked twice by investigators after the data is entered. The collected clinical data will be entered into the database and the database will be regularly updated according to follow-up timing. The original CRF and all database data will be securely stored in the Oncology Department building at Zhongshan Hospital of Traditional Chinese Medicine affiliated to Guangzhou University of Chinese Medicine. Throughout the trial, two trained, qualified, and independent supervisors will regularly visit the trial center to be responsible for data monitoring, regulatory management, and to conduct a trial audit every 3 months, independent of the investigator and the organizer. This will include specification of the random inspection program, the reasonableness of the inclusion and exclusion criteria, the proper implementation, the implementation of informed consent procedures, the specification of the CRF, the confidential updating of the database, and SAE reporting, and also determining whether to terminate the study prematurely. For any cases in which there is shedding or loss of visit, it will be necessary to explain the reasons for the shedding and the loss of visit, and calculate the proportion of cases in which there was shedding and loss of visit relative to the total number of observed cases.

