## Conclusion

mCRC patients after reaching NED state still lack an effective standard therapy, and thus the proposed study will primarily observe capecitabine metronomic chemotherapy for mCRC after reaching NED state maintenance treatment regarding the DFS, OS, the quality of life score and adverse reaction data. This study is expected to change clinical guidelines, to provide high-quality clinical research data for clinical practice of such patients.

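### Survival follow-up stops at month 36 for each patient, so later deaths in early-enrolled patients are lost to the OS analysis; one common closing date would recover them cheaply

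*Protocol article*

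**What the plan says.** The abstract (Methods/design) says "All participants will follow up for 1 year after receiving 2 years of intervention". The Intervention section repeats it: "Follow-up will last for 12 months, beginning after the completion of the 24-month intervention period", and adds "The study will be conducted over a 3-year period, with all treatments completed within the first 2 years". The two group descriptions give the same 2 years plus 1 year. Survival rates are to be read "at the time nodes of the 1^st^ year, 2^st^ year and the 3^nd^ year after randomization", so year 3 is the last survival time point. No survival contact after month 36 is described.

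On the calendar, Study subjects says "It will be conducted from December 2021 to December 2025". Trial status gives 31 December 2021 to 31 December 2025 and says recruitment is still open. Statistical analysis places the confidence interval for the hazard ratio at the end of the trial.

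On OS, the Introduction reports that adjuvant chemotherapy prolonged DFS in two earlier trials; "however, no significant enhancement in overall survival has been observed". OS is secondary in the abstract and under Outcome, yet the OS paragraph itself calls it a further primary outcome. That paragraph also sets the time of death of a patient lost to follow-up at the last follow-up. Quality control mentions contact with the patient and a family member, and that "regular telephone follow-up was conducted". The Conclusion says "This study is expected to change clinical guidelines".

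**The concern.** A fixed 36-month window per patient suits a 3-year DFS comparison. For OS it discards information. A patient randomised on 31 December 2021 leaves follow-up on 31 December 2024, a year before the stated end of the trial. A death in that year is not recorded, although the final hazard ratio has not yet been computed.

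The plan's own background makes OS the natural next question after a positive DFS result, and the Conclusion hopes to influence guidelines. The OS interval will be wide whatever is done. Leaving out deaths that a telephone call would establish makes it wider than it need be.

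**Working it through.** **Plan's own figure.** The protocol states no OS rate, no expected number of deaths and no OS power, so there is no OS figure to reproduce. The sample size rests on DFS alone.

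**A ceiling on deaths from the plan's own numbers.** Inputs: 120 patients per arm (Study design); 3-year DFS of 52.1% and 67.1% (Sample size calculation); death from any cause is a DFS event (Primary outcomes).

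- Expected DFS events by month 36: 120 × (1 − 0.521) + 120 × (1 − 0.671) = 57.5 + 39.5 ≈ 97. Expected deaths by then cannot exceed this.
- Implied DFS hazard ratio: ln(0.671)/ln(0.521) = 0.612.
- Deaths needed for 80% power, two-sided 0.05 (Schoenfeld): 4 × (1.96 + 0.8416)² / (ln 0.612)² ≈ 131.
- If all 97 events were deaths, OS power would be about 68% at 0.612, 29% at 0.75 and 19% at 0.80.

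**What a common closing date adds.** Assumptions, not in the documents: 3-year OS of 75%, 80% or 85% over both arms, constant hazard, uniform accrual over A years, no losses.

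- λ = −ln(OS₃)/3.
- Deaths with the month-36 stop: 240 × (1 − OS₃).
- Deaths with everyone followed until the last patient's month 36: 240 × {1 − [exp(−3λ) − exp(−(3+A)λ)]/(λA)}.
- 95% CI = HR multiplied or divided by exp(1.96 × 2/√deaths).

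| Assumed 3-year OS | Stop at month 36 | Common date, A = 1 | A = 2 | A = 3 |
|---|---|---|---|---|
| 75% | 60 (1.66) | 68 (1.61) | 76 (1.57) | 84 (1.54) |
| 80% | 48 (1.76) | 55 (1.70) | 62 (1.65) | 68 (1.61) |
| 85% | 36 (1.92) | 41 (1.84) | 47 (1.78) | 52 (1.72) |
| More deaths | – | 14-15% | 27-30% | 39-44% |

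Entries are deaths, with the CI factor in brackets.

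**If 31 December 2025 is a hard stop.** With entry spread over A years from 31 December 2021, follow-up ranges from 4 − A to 4 years. I compared deaths with and without the 36-month cap inside that window. Lifting the cap adds 14-15% with 1-year accrual, 7-8% with 2-year and 5-6% with 3- or 4-year accrual. At 80% OS and 2-year accrual this is about 44 against 48 deaths.

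**Calendar check.** 31 December 2025 minus 36 months is 31 December 2022. Anyone enrolled later cannot complete month 36 before the stated end.

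**The case against.** OS is listed as secondary, no OS power is claimed, and 36 months matches both the DFS assumption and the last survival time point, so the window is a coherent choice for the primary question. That stands, and it is why this is an improvement and not an error in the primary analysis.

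The remedy does not make OS conclusive. That also stands: at an assumed 80% OS the CI factor falls only from 1.76 to 1.65 (2-year accrual) or 1.61 (3-year).

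The larger gains need closure in December 2026 or 2027, dates the protocol does not give. Within the stated 48 months the gain is about 5-15%. This is correct, so both ranges are shown.

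The telephone contact is described as a means to improve compliance, not as survival follow-up. True, so its use for survival status must be written in.

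A reader might infer that OS will be analysed while the trial is still running. The documents do not support that: the hazard ratio is placed at the end of the trial, and what stops early is data collection on early patients. A reader might also infer that a DFS gain will be presented as a survival benefit. No section says so.

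**Conclusion.** The point holds as a modest, low-cost improvement. The 36-month stop is explicit, and nothing in the text provides for survival status afterwards. The gain is 14% to 44% more deaths for accrual of 1 to 3 years with a closing date at the last patient's month 36, or about 5-15% if collection ends on 31 December 2025. These figures rest on an assumed 3-year OS of 75% to 85%, constant hazard and uniform accrual. Only the ceiling of about 97 deaths comes from the plan's own figures, and it shows that OS should be reported as a hazard ratio with its confidence interval, not as a powered test.

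Two related passages bear on it. Read literally, the OS rule for lost patients turns each loss into a death, so longer follow-up could add false deaths along with real ones. And the stated trial end is incompatible with 36 months of follow-up for anyone enrolled after December 2022; if that date is binding, later patients are cut off sooner and deaths are fewer still.

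**What to change.** 1. Leave the DFS visits and the 36-month DFS analysis as they are.
2. For OS, replace the per-patient stop with one closing date, when the last randomised patient reaches month 36. Until then, collect survival status and date of death on every randomised patient by telephone, and state this purpose in the protocol.
3. Use all of this follow-up in the OS curves, log-rank test and hazard ratio. Censor patients lost to follow-up at last contact.
4. Describe OS consistently as a secondary endpoint, reported as a hazard ratio with its confidence interval, and remove the wording that calls it a primary outcome.
5. Reconcile the stated end of the trial with 36 months of follow-up for patients enrolled after December 2022, saying whether December 2025 closes recruitment or the study.

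Cost: protocol wording, further telephone calls to early-enrolled patients, and an ethics or consent amendment if consent covers only 36 months. OS results may come later than under the per-patient stop if the closing date falls after December 2025. No extra patients, scans or clinic visits are needed.

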**Discussion:**

As a potentially effective treatment, low-dose capecitabine metronomic chemotherapy has been explored in clinical practice. The results of this trial will provide evidence on the efficacy and safety of capecitabine metronomic chemotherapy for patients with mCRC who have reached NED status.

**Trial registration:**

Chinese Clinical Trial Registry (ChiCTR2100047149, protocol version number F2.0)

## Introduction

Metastatic colorectal cancer (mCRC) accounts for more than 40% of the total colorectal cancer population [1,2]. In recent years, with the progress of surgery and a series of drugs to improve the objective response rate of tumors, more and more patients with mCRC can now receive surgical resection after conversion therapy, or achieving no evidence of disease (NED) status through local treatment such as ablation [3,4]. This has greatly improved survival for patients with mCRC. At present, a total of 6 months of perioperative chemotherapy is routinely recommended for patients with mCRC after resection, but many patients have postoperative recurrence and metastasis. For patients with mCRC who achieve NED status after resection, how to avoid tumor recurrence and metastasis after surgery is an urgent clinical problem [5,6].

Approximately 60–70% of patients diagnosed with stage IV colorectal cancer will experience tumor recurrence and metastasis following surgical intervention. Previous studies(JCOG0603, EORTC40983) have demonstrated that adjuvant chemotherapy following surgical intervention for metastatic colorectal cancer is associated with a prolonged duration of disease-free survival (DFS); however, no significant enhancement in overall survival has been observed [7,8]. The presence of Minimal Residual Disease (MRD) or Circulating Tumor Cell (CTC) significantly contributes to the postoperative recurrence of colorectal cancer. The efficacy of adjuvant chemotherapy may be compromised by drug resistance and the immunosuppressive microenvironment within the human body, necessitating the development of novel therapeutic approaches.

Fluorouracil (5 - FU) is the most important and basic drug used in chemotherapy for colorectal cancer. Capecitabine is an oral drug and a member of the fluorouracil class. The highly expressed thymidine phosphorylase in tumor tissue can degrade it into 5-FU, significantly increasing the drug concentration at the tumor site, and simulating continuous perfusion of 5-FU, so that it maintains a stable blood drug concentration at the action site [9]. Single-agent capecitabine is commonly administered to mCRC patients who exhibit intolerance towards multi-drug combination chemotherapy. However, the conventional dosage (Capecitabine 1250mg/m^2^ body surface area twice daily) poses challenges such as significant toxic reactions, immunosuppression, and drug resistance [10,11].

Capecitabine metronomic chemotherapy is a mode of small dose, continuous administration and oral administration which can maintain drug concentration at a low and effective blood drug concentration for a long time, prolong the disease control time, and mitigate the toxic side effects. Metronomic chemotherapy exerts an anti-tumor effect by inhibiting tumor angiogenesis, and can promote and induce anti-tumor immune response in the microenvironment. Its targets are vascular endothelium and tumor stromal cells, tumor stem cells and immune cells, but not the tumor itself. It can shorten the treatment interval, reduce the recovery time for tumor cells during the treatment interval, and inhibit tumor proliferation by anti-angiogenesis, immune activation, reducing drug resistance and inducing tumor dormancy to inhibit tumor proliferation [12–16].

After multiple courses of combined chemotherapy for advanced colorectal cancer, patients’ sensitivity to drugs will decline, and the adverse reactions of the chemotherapy drugs will continue to accumulate. It is necessary to balance the anti-tumor effect while reducing the treatment-related adverse reactions. Capecitabine metronomic chemotherapy has shown good efficacy in breast cancer and head and neck cancer [17]. The SYSUC-001 study [18] analyzed the efficacy of capecitabine metronomic chemotherapy after standard treatment in patients with triple-negative breast cancer. 434 patients were randomized to either a capecitabine metronomic chemotherapy group (650 mg/m^2^ twice daily for 1 year) or an observation group. The findings showed that 5-year DFS significantly improved in the capecitabine metronomic chemotherapy group versus the observation group (83% vs. 73%). A multicentre, randomised, controlled, phase 3 trial have shown that capecitabine metronomic chemotherapy improved failure-free survival in patients with high-risk locoregionally advanced nasopharyngeal carcinoma [19]. However, there is currently a lack of prospective randomized controlled trials (RCTs) assessing the efficacy and safety of capecitabine in patients with mCRC following achieving NED status. The purpose of this trial is to evaluate the effect of capecitabine metronomic chemotherapy for mCRC patients reaching NED state.

